### Baseline testing and intervention

Baseline testing will take place over two visits. During the second baseline visit, components of the intervention will be introduced.

### Baseline visit 1

During Baseline Visit 1, anthropometric measurements of height, weight and waist circumference will be taken. To assess body composition participants will undergo dual energy x-ray absorptiometry (DXA) testing. The DXA scan uses a low emission x-ray in conjunction with Hologic software to provide measurements for lean mass, fat mass and bone mineral density (Hologic QDR 4500, Hologic, Inc., Bedford, MA).

#### Blood collection

All blood draws will be performed after an 8 hour overnight fast by a trained nurse or phlebotomist. 2 ml of blood will be collected with sodium fluoride for glucose analysis. A further 3 ml of blood will be collected in serum tubes for adipokine analysis (adiponectin, c-reactive protein (CRP), leptin, IL-1β, IL-6, IL-8, TNF-α, MCP-1 and insulin). A final 4 ml will be collected for serum lipid analysis. Samples will be centrifuged and stored at -80°C until analysis.

#### Plasma glucose

Blood glucose concentrations will be measured in triplicate using a glucose trinder assay kit (Stanbio Laboratory, Boerne, TX). Serum Adipokines: Adiponectin will be measured in duplicate using an ELISA kit from Millipore (Millipore, Billeerica, MA). For leptin, IL-1β, IL-6, IL-8, TNF-α, MCP-1 and insulin duplicates samples of 25 μl of serum will be analyzed using a Milliplex MAP Human Serum Adipokine Panel B kit (Millipore, Billerica, MA). CRP will be measured by Calgary Laboratory Services (Calgary, AB). Serum lipids: 1.5 ml of serum will be sent to Calgary Laboratory Services for quantification (total cholesterol, HDL cholesterol, LD cholesterol and triglycerides will be calculated).

#### 7-day activity monitoring

Participants will be provided with an activity monitor (Actigraph GT3X, Actigraph LLC, Pensacola, FL.) and an activity log. Participants will be instructed to wear the monitor during the waking hours, except when in contact with water. Participants will also be instructed how to complete a daily log to accompany the activity monitor. Participants will be asked to wear the monitor for the 7 days following Baseline Visit 1, to establish baseline activity level (steps per day). The activity monitor can provide an objective record of frequency, intensity, and duration of physical activity with minimal burden on participants. The Actigraph is widely accepted in the field as a valid and reliable means of assessing ambulatory physical activity [32-36].

#### 3-day food records

Food and beverage intake will be assessed using 3-day food records. Participants will be trained on how to complete a 3-day food record by a Registered Dietitian on their first visit. Participants will then be asked to estimate portion sizes and record all food and beverages consumed for 2 weekdays and 1 weekend day. The food record will be completed in the week following Baseline Visit 1, to establish baseline dietary intake. Dietary intakes will be analyzed with Diet Analysis Plus 10.0 software (Thomson Wadsworth, Toronto, ON).

Participants will be provided with a self-addressed, stamped envelope to return the activity monitor, activity log, and 3-day food record to Mount Royal University.

### Baseline visit 2

Baseline testing during Baseline Visit 2 will include questionnaire completion, a Self-Paced Walking Test, balance testing, a neurological examination, and peak VO_2_ exercise test on a cycle ergometer. Intervention components of Baseline Visit 2 will include a one hour personalized consultation session with a Registered Dietitian, and a one hour personalized physical activity counseling session with an Exercise Physiologist (including instructions regarding how to use the pedometer). Participants will also be guided through the process of initial login and navigation of the e-health intervention website, as well as provided with instructions regarding how to fill out the daily personal log book.

#### Baseline testing details

##### Questionnaire

The questionnaire will be used to collect information regarding age, gender and history of back and leg pain, as well as history of medications, alcohol use, tobacco use and current work status. The standardized instruments to be used can be found in Table 1. The questionnaire will be completed online through the intervention website.

**Table 1 T1:** Standardized questionnaires

**Questionnaire**	**Description**
Physical Function Scale of Swiss Spinal Stenosis Questionnaire (PF Scale) [1]	The Physical Function Scale was designed to assess walking capacity in people with LSS. The score is calculated as the un-weighted mean of the five items in the scale. The resulting possible scores of 1–4 represent a range from mild to severe limitation in physical function/walking.
Symptom Severity Scale of the Swiss Spinal Stenosis Questionnaire (SS Scale) [1]	The Symptom Severity Scale of the SSSQ was designed to examine severity of symptoms related to LSS. It is scored as the un-weighted mean of the seven items in the scale, with scores from one to seven representing a range from mild to very severe pain.
Oswestry Disability Index (ODI) [37]	The ODI is a nine-item questionnaire, which assesses degree of back pain–related disability. Severity of pain and disability in activities, such as walking, sitting, standing, and personal care, are rated on Likert scales of five or six points. The ODI was calculated as a percentage of the total possible score of 53, with a greater score representing greater back pain–related disability.
Short-Form 36 (SF-36) [38]	Overall health and disability will be assessed using the 36-Item Short Form Health Survey. Using the 36 items, the following scales are calculated: General Health, Physical Functioning, Social Functioning, Role Limitation—Physical, Role Limitation—Emotional, Mental Health, Vitality, and Bodily Pain. Each scale score is calculated independently using algorithms defined by the developers.
Centres for Disease Control Depression Scale (CES-D) [39]	The 20 item Centres for Epidemiologic Studies Depression Scale was designed to assess depression. It is scored by totaling all item scores, with a higher total indicating greater depression. Scores range from 0 to 60, with higher scores indicating more symptoms of depression. CESD scores of 16 to 26 are considered indicative of mild depression and scores of 27 or more indicative of major depression.
Regulation for Eating Behaviors Scale (REBS) [40]	To assess healthy eating motives, participants will complete the 24-item Regulation of Eating Behaviour Scale. Six subscales comprised of 4 items/subscale formulate the REBS including (a) Amotivation, (b) External Regulation, (c) Introjected Regulation, (d) Identified Regulation, (e) Integrated Regulation, and (f) Intrinsic regulation. Participants respond to each REBS item on a 7-point Likert scale anchored at the extremes by (1) 'Does not correspond at all’ and (7) 'Corresponds exactly’.
Behavioral Regulation in Exercise Questionnaire 2-R (BREQ-2R) [41,42]	•To assess exercise motive related to exercise, participants will complete the 19 item Behavioral Regulation in Exercise Questioniare-2 plus four items assessing Integrated Regulation. The BREQ-2 assesses the following constructs: (a) Amotivation, (b) External Regulation, (c) Introjected Regulation, (d) Identified Regulation, and (e) Intrinsic Regulation. Reponses to the BREQ-2 and Integrated Regulation items were made using a 5-point Likert scale anchored at the extremes by 0 ('Not true for me’) and 4 ('Very true for me’).
Pain Catastrophizing Questionnaire [43]	The PCS was designed to assess pain catastrophizing. The PCS is a 13-item instrument that asks participants to reflect on past painful experiences, and to indicate the degree to which they experience each of 13 thoughts or feelings when experiencing pain, on 5-point scales with the end points (0) not at all and (4) all the time. The PCS total score is computed by summing responses to all 13 items. PCS total scores range from 0 – 52. A score of 30 or above represents clinically relevant catastrophizing.
Tampa Scale for Kinesiophobia (TSK) [44,45]	The TSK was designed to assess fear of movement (kinesiophobia). The TSK uses a 4-point Likert scale, with scoring options ranging from 1 = 'strongly disagree’ to 4 = 'strongly agree’. A total score is calculated after inversion of the individual scores of items 4, 8, 12 and 16. The total score ranges between 17 and 68. A high value on the TSK indicates a high degree of kinesiophobia. A score of 37 differentiates between high and low scores.

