### Testing schedule

Following enrollment, patients will begin the study protocol, which involves 7 testing appointments over a 6 month period. These appointments include Baseline Visit 1 (week -1), Baseline Visit 2 (week 1), 6-week check-in (week 6), Follow-up Visits 1 and 2 (week 13) and Follow-up Visits 3 and 4 (week 24). The intervention begins at Baseline Visit 2 and runs for 12 weeks (weeks 1–12). Enrollment will be continuous throughout the study. Once patients are enrolled they will begin assessments at the next available scheduled date for Baseline Visit 1. Six-week check-in sessions will be arranged individually for each participant. The primary outcomes at each time point will be fat mass (%), steps/day, and quality of life (SF-36).

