### Statistical analysis

Using the raw quantitative data from the participants of both groups we will present descriptive statistics summarizing the mean and standard deviation with respect to all the primary study variables. Age and sex distributions of the participants will be tabulated. Our goal is to establish reliable point estimates of the study variables and to characterize the variability within the two groups.

The independent variable will be the intervention, while the dependent variables will include steps/day, fat mass (%) and health related quality of life (SF-36 overall score). Linear mixed-effects models will be used to determine whether the changes for each time period (baseline to 13 weeks, baseline to 24 weeks) were significantly different between intervention and control groups. Repeated measures analysis of variance (RANOVA) will be used to examine within group changes from baseline to 13 weeks and from baseline to 24 weeks.

We will also examine changes in the following variables: Biochemical markers of obesity and associated co-morbidities including Plasma glucose, Serum adipokines (c-reactive protein (CRP), leptin, IL-1β, IL-6, IL-8, TNF-α, MCP-1 and insulin), and Serum lipids (total cholesterol, LDL cholesterol, HDL cholesterol and triglycerides); Physical function (Physical Function Scale of Swiss Spinal Stenosis Questionnaire); Walking capacity (Self-Paced Walking Test distance); Balance (mean deviation from centre of pressure from balance platform); Neurological impairment (Neurological Impairment Score); Pain (Symptom Severity Scale and visual analog scales); Back pain related disability (Oswestry Disability Index); Fear of movement (Tampa Scale for Kinesiophobia); Depression (CES-D total score); kilocalorie intake (kcal/day); Fat intake (grams/day); Vegetable and fruit intake (Canada Food Guide servings/day); Fibre intake (grams/day); and Change questions for activity, mood, overall health, calories, vegetable intake, and fibre intake. Clinical MRIs we will be used to assess whether imaging findings are predictive of change in the primary outcome variables following the intervention.

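### The Oswestry percentage divides by a maximum of 53 without subtracting the minimum of 9 that this maximum implies, so no disability is reported as 17.0% and changes as 0.83 of their zero-based size

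*Protocol article*

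**What the plan says.** The scoring rule is in the protocol article, Table 1 (Standardized questionnaires), in the ODI row. It gives three figures:

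- Number of items: "The ODI is a nine-item questionnaire, which assesses degree of back pain–related disability".
- Response format: the items "are rated on Likert scales of five or six points".
- Score: "The ODI was calculated as a percentage of the total possible score of 53", "with a greater score representing greater back pain–related disability".

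The row does not say whether item codes start at 0 or at 1, how many items have five points and how many six, or what the lowest score is. Nor does it claim that the percentage runs from 0 to 100.

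The Statistical analysis section lists "Back pain related disability (Oswestry Disability Index") among the further variables to be examined for change. The Follow-up section repeats the baseline questionnaire at weeks 13 and 24. The ODI is not a primary outcome. The Testing schedule section says: "The primary outcomes at each time point will be fat mass (%), steps/day, and quality of life (SF-36").

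**The concern.** A disability score given as a percentage invites the reader to take 0% as no disability and 100% as the worst state. Dividing the raw sum by the largest possible sum gives that scale only if the smallest possible sum is zero. If each item's lowest code is 1, nine items cannot sum to less than 9, and the percentage starts well above zero.

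The reported figures are at stake, not the test. Baseline disability would look higher than on a zero-based scale, and changes and between-group differences would look smaller. Someone setting these results beside a zero-based ODI percentage would be misled without warning, because the table gives no minimum. Elsewhere Table 1 does give score ranges for summed instruments: 0 to 60 for the CES-D, 0 to 52 for the PCS, and 17 to 68 for the TSK, whose non-zero floor is thereby disclosed. The ODI is turned into a percentage, but no floor is given.

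**Working it through.** **Inputs, all from the ODI row of Table 1:** 9 items; 5 or 6 response points per item; denominator 53.

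**Assumptions, not stated in the document:** each item takes consecutive whole-number codes starting at 0 or at 1, and the lowest code means no disability on that item.

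**Step 1: reproduce 53.** Let k items have six points and 9 − k have five.

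- Coded from 0: minimum 0, maximum 5k + 4(9 − k) = 36 + k. With k from 0 to 9 the maximum lies between 36 and 45. Reaching 53 would need k = 17, which is impossible with nine items.
- Coded from 1: minimum 9, maximum 6k + 5(9 − k) = 45 + k. Setting 45 + k = 53 gives k = 8.

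So 53 is reproduced in exactly one way: coding from 1, eight six-point items and one five-point item, 8 × 6 + 1 × 5 = 53. This agrees with the table's mention of both five- and six-point items.

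**Step 2: range of the stated score.** Raw totals run from 9 to 53.

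- Floor: 9/53 = 17.0%.
- Ceiling: 53/53 = 100%.
- Usable span: (53 − 9)/53 = 44/53 = 83.0%.

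**Step 3: compare with a zero-based percentage.** Let S be the raw sum, stated score = 100 × S/53, and zero-based score = 100 × (S − 9)/44. Substituting one into the other:

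stated score = 17.0 + 0.83 × zero-based score

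| Raw sum | Stated rule | Zero-based rule |
|---|---|---|
| 9 (no disability) | 17.0% | 0% |
| 31 (mid-scale) | 58.5% | 50% |
| 53 (worst) | 100% | 100% |

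The constant 17.0 cancels in any change or difference, leaving the factor 0.83. A change of 10 points on the zero-based scale is reported as 10 × 0.83 = 8.3 points, a shrinkage of 17.0%.

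**Step 4: effect on inference.** The stated score is a linear function of the zero-based score, with the same constants in both groups and at every visit. Mean differences, standard deviations and standard errors are all multiplied by 0.83. Their ratios are therefore unchanged, and so are p-values, standardised effects and power. The sample size rests on steps and does not use the ODI.

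**The case against.** The strongest reply is that the three stated figures agree with each other. Nine items, five or six points and a maximum of 53 fit exactly when coding starts at 1, and the raw sum divided by 53 is literally a percentage of the total possible score. The row promises neither a 0–53 nor a 0–100 range. The table is also a condensed instrument summary citing its source, its scoring sentence is in the past tense, and item coding is the sort of detail a fuller document would hold.

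Much of this stands. A reader might infer that 53 is an arithmetic slip or an unreachable total. The document does not support that: 53 is unreachable only under coding from 0, and the stated figure itself excludes that coding. A smaller shrinkage of about 15% (1 − 45/53) is likewise unsupported, because it needs nine six-point items coded from 0, whose maximum is 45 and not 53.

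A reader might also infer that the ODI treatment effect will be wrong. That goes too far. The protocol sets no ODI threshold, important difference or responder definition that the scaling would break, and a result can be converted exactly once the coding is known. Nor does the missing statement of coding count as a fault in itself.

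What remains is that the article does fix a scoring rule. On the only coding that fits its own maximum, that rule leaves in a floor of 9 that the reader is not told about.

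**Conclusion.** The point holds as a scoring and reporting defect of limited reach. On the coding that reproduces 53, the stated percentage runs from 17.0% to 100%, and absolute changes are 0.83 of those on a zero-based percentage scale. Only the reported ODI level, its change in percentage points, and comparison with a zero-based percentage are affected. No test result and no primary outcome is touched.

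The size depends on the assumption of consecutive integer codes and on reading 53 as the true maximum of the form in use. If the form's maximum were something else, the denominator itself would need correcting. In no case could nine five- or six-point items give a 0–100% scale on division by 53, since their span is at most 45 units.

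**What to change.** In the ODI row of Table 1, or in the scoring section of the analysis plan:

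1. State the item coding, the number of five- and six-point items, and hence the minimum and maximum sums.
2. Replace the rule with score = (sum − minimum)/(maximum − minimum) × 100. For the form whose maximum is 53 this is (sum − 9)/44 × 100.
3. Apply it identically at baseline, week 13 and week 24, and say that 0% is no disability and 100% the worst score.

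The general formula is right under either coding, so it is safe even if the form turns out to be coded from 0.

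The cost is one line of scoring text. No new data are needed, and the rule can be applied to responses already collected. A complete-questionnaire score P already computed on the stated rule converts exactly: raw sum = 53 × P/100, then subtract 9, divide by 44 and multiply by 100.

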##### Self-paced walking test

All participants will undergo a standardized Self-Paced Walking Test [46]. This test has been shown to be a valid criterion measure of walking capacity in people with LSS. Participants are instructed to walk continuously at their own pace until they feel that they have to stop due to symptoms of LSS (or other reasons) or until a time limit of 30 minutes has been reached. Participants are asked to indicate when they first experience a change in symptoms, as well as to indicate the nature of the symptoms (type and location). Test termination is defined as a complete stop of 3 seconds or more. The following information is collected: total distance and time walked, time/distance to onset of symptoms, the nature and location of symptoms (pain, numbness/tingling, weakness or fatigue), average walking speed, and the reason for test termination should they not walk for the full 30 minutes (symptoms of LSS, fatigue, shortness of breath, dizziness, pain or discomfort due to co-morbidities). Before and immediately after the walking test, participants will be asked to rate their current pain on 100 mm Visual Analog Pain Scales for back, right leg and left leg, with anchors of 0 (no pain) and 10 (worst possible pain). VAS scales have been used often in research with spinal stenosis patients and found to be psychometrically sound [47,48]. Participants will also be asked to indicate on a body diagram the location and nature of their symptoms.

##### Balance testing

Balance will be assessed using a HUR-3 Balance platform. Each participant will be assessed for 20 seconds on each of the following stances (all with eyes open and a firm surface): double leg stance, tandem stance with right leg forward, tandem stance with left leg forward, single leg right, single leg left. For each test, participants will be asked to place their hands on their hips and face forward. Balance test results are stored using the HUR-3 software.

##### Neurological impairment score [49]

Both lower limbs are tested and five parameters are assessed. Points are added up to a maximum total score of 33 (with a higher score indicating less neurological impairment). 1. Tendon (myotatic) reflexes in lower limbs, that is, patellar reflex and Achilles tendon reflex. For each reflex evoked (using facilitating manoeuvres), the person examined is given 1 point, potential score 0–4 points. 2. Tactile sensation in lower limbs using a cotton swab. If there is a dysfunction of tactile sensation in both lower limbs, the person examined receives 0 points. If there is a dysfunction of tactile sensation in only one lower limb then the score is 2 points. If tactile sensation is bilaterally normal, the score is 4 points. 3. Vibration sensation in the lower limbs will be assessed using a 128-Hz graduated tuning fork for optimum accuracy. The vibration threshold is recorded on a scale from 0 to 8, with the maximum expressed as 8/8 and minimum 0/8. Vibration sensation will be recorded at the external ankle. 4. Presence of paresis of lower limbs will be assessed by asking the participant to stand on tiptoe, stand on the heels, and squat. Each exercise successfully performed scored 1.5 points (giving a total range of 0–9 points). Squatting is considered as the ability to stand from a full squatting position. Whenever the results of these tests are in doubt (e.g., where the influence of pain or joint arthrosis appeared possible), the presence of paresis will be verified by isometric muscle testing. 5. Evaluation of ability to walk and run. If the participant is able to run at least 10 m, 12 points will be awarded. If the person is able to walk this distance without support he/she receives 9 points. Walking with one crutch will score 6 points, walking with the aid of two crutches will score 3 points. If the participant is unable to walk, the score will be 0.

##### VO_2peak_ testing protocol

The test administrator will review the participant’s medical history, physical findings and check for any absolute contraindications to exercise, or signs indicative of major cardio-vascular, pulmonary or metabolic disease. All tests will be conducted by a Certified Exercise Physiologist or Kinesiologist. Prior to exercise testing, height and weight will be measured, and 12-lead electrocardiogram (ECG) electrodes placed. The BORG scale for perceived exertion (RPE) will be explained to the participant [50]. Resting heart rate, blood pressure and ECG readings will be obtained over 4 minutes prior to testing [51-54]. The participant will be set up at the appropriate seat height on an electrically braked cycle ergometer. A face mask will be connected to a metabolic cart for breath by breath gas analysis. The ECG will remain connected to a three channel recorder for ECG, time and ventilation recordings [55]. The following variables will be recorded in the last 15 seconds of each minute during 4 minutes of unloaded cycling, before and after the test, and during the last 15 seconds of each stage in the incremental protocol to follow: heart rate, ventilation, volume of oxygen (VO_2_), volume of carbon dioxide, and respiratory exchange ratio (RER) [51,56]. Blood pressure will be measured before and after the test, as well as in the last 15 seconds of each third minute [54]. RPE will be measured in the last 15 s of each third minute. Throughout the test the ECG will be monitored for abnormal changes.

The individualized incremental protocol to be used is taken from Wasserman et al. [56] and has been found to produce accurate estimates of VO_2 peak_[56]. For each participant, VO_2_ unloaded is calculated from the participant’s weight, and VO_2peak_ is estimated from the participant’s age and height [56]. The work rate increment necessary to reach the estimated VO_2peak_ in 10 minutes is calculated. This time limit is chosen because it has been shown that incremental tests of 6–12 minutes provide the highest VO_2peak_ for normal participants [56].

1. VO_2_ unloaded in ml/min = 150 + (6 × weight in kg)

2. VO_2_ peak in ml/min = (height in cm ‒ age in years) × 20 for sedentary men and × 14 sendentary women

3. Work rate increment per minute in watts = (VO_2_ peak estimate ‒ VO_2_ unloaded estimate)/100

After 4 minutes of unloaded cycling, the calculated work load is applied increased by that amount every minute until a symptom limited test endpoint is reached. Participants will be encouraged to continue until they feel that for whatever reason, they are unable to. Once the test is terminated, the participant will continue unloaded cycling for 4 minutes. The participant will be asked to indicate what symptoms caused he/she to stop the test [56]. All variables will continue to be measured as described during this time. The ECG, blood pressure and RPE will be monitored every minute until values return to baseline [52].

VO_2peak_ will be determined as the highest value for VO_2_ averaged over a 30 second period [54], and will be confirmed by any of the following criteria [52]: Failure of heart rate to increase with increasing load, or achievement of 85% age predicted max heart rate; a plateau in oxygen uptake with increasing work-load; RER of >1.15; RPE > 17 on the BORG scale.

